| GENERAL OBJECTIVE      | To evaluate the difference in days of invasive mechanical ventilation between early multimodal therapy and late multimodal therapy in the adult intensive care unit of the Santa Fe Foundation in Bogotá.                                                                                                                                                                                                                                                                                                                                                                                                                                                                                                                                                                                                                                                                                                                   |
| SPECIFIC OBJECTIVES    | 
To describe the sociodemographic and clinical characteristics of patients with invasive mechanical ventilation in the Adult Intensive Care Unit of the Santa Fe Foundation in Bogotá.
 
To evaluate the effectiveness of early multimodal therapy versus late multimodal therapy in terms of ventilator-free days and other secondary outcomes.
 
Establish the sociodemographic and clinical factors that are associated with the type of therapy (early or late) and with the primary outcome (days free of mechanical ventilation) and secondary outcomes.
 
To evaluate the safety of early multimodal therapy versus late multimodal therapy in terms of adverse events, serious adverse events, episodes of aspiration, and healthcare-associated pneumonia.
 
To evaluate the impact of the different previously defined subgroups, such as the type of respiratory failure (hypoxemic or
 |

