| STATISTICS, PRIMARY PLAN OF ANALYSIS                              | 
A Shapiro-Wilk test will be performed to verify the distribution of the quantitative variables, considering the number of patients included. Data will be presented as means or medians, accompanied by their standard distribution or interquartile range, as appropriate. Categorical variables will be described as absolute and relative frequencies.
 
To compare continuous variables between the two groups (early vs. late therapy), a T-test or the Mann-Whitney U test will be used, depending on the distribution of the data. For categorical variables, a <math>\chi^2</math> test or Fisher's exact test will be used, as appropriate.
 
The primary objective of the study is to evaluate the association between the use of early multimodal therapy and days of invasive mechanical ventilation. To answer this question, we will perform a survival analysis and Cox regression. A risk variable will be created by combining the time of invasive mechanical
 |

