|  | 
potentially interact. If the regression coefficient of this new variable has a significance level of less than 0.05, it is concluded that there is an interaction and said variable will be included in the model. Variables with interaction potential will be identified by assessing confounding factors. The investigators will also evaluate clinical variables that may be considered as interaction or confounding variables through the strategy described above.
 
Compliance with the assumption of risk proportionality will be evaluated using Schoenfeld residuals and influential values will be analyzed using graphs of residuals versus observations. Multicollinearity will be evaluated through matrix curves.
 
We will use logistic regression models to assess the relationship between our dichotomous variables, such as failed extubation, post- extubation NIV, prolonged mechanical ventilation, tracheostomy and dysphonia, and the other variables studied. The assumptions of a logistic regression model, such as linearity in the log of probabilities, independence of errors, homogeneity of variance, absence of multicollinearity, absence of outliers, and proportionality of effects, will be evaluated through residual analysis and graphical diagnostics, such as Pearson residual analysis or deviance residual analysis.
 
A multiplicity adjustment strategy will be used in statistical tests, such as the Bonferroni method, Holm-Bonferroni, or other methods that control the false discovery rate (FDR), to maintain the overall type 1 error rate at an acceptable level.
 
We will carry out a detailed exploration through a sensitivity analysis of possible interactions between the identified subgroups, according to the RASS scale, according to adherence
 |

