| Comparator | Late multimodal therapy is defined as the initiation of multimodal therapy 3 days or more after the start of mechanical ventilation. The comparator differs from the study intervention only in the moment (time from orotracheal intubation to the start of multimodal therapy) of initiation of therapy.                                                                                                                                                                                                                                                                                                                                                                                                                                                                                                                                                                                                                                                                                                                                      |
| Outcomes   | 
Effectiveness
 
Primary outcome: Number of days with invasive mechanical ventilation in the ICU
 
Secondary outcomes:
 
 
• Days free of mechanical ventilation until day 28
 
• Days of delirium until day 28
 
• Time in ICU with delirium until day 28
 
• Days of hospitalization with delirium until day 28
 
• Sedation days until day 28
 
• Sedation-free days until day 28
 
• Barthel index at discharge
 
• Days of hospital stay
 
• Length of stay in ICU
 
• Mortality from any cause up to 90 days
 
• Time from intubation to start of therapy
 
• Muscle strength measured with the medical research scale council (MRC)
 
• Dysphagia at 72 hours
 
• Time until initiation of oral administration
 
• Development of healthcare-associated pneumonia,
 
• Maximum mobility measured by JH-HLM
 
• Grip strength
 
• Extubation failure
 
 |

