### 6.3. Sample size

Based on the study published by Schweickert et al. where they found that the mean number of days of mechanical ventilation in patients with usual physical therapy was  $6.1 \pm 1.4$  days and in early therapy it was  $3.4 \pm 1.25$  days (32), for an alpha error of 0.05 and a statistical power of 0.8 is considered the following formula:

$$ES = \frac{|\mu_1 - \mu_2|}{\sqrt{DE1^2 - DE2^2/2}}$$

$$ES = \frac{|6.1 - 3.4|}{\sqrt{1.40^2 - 1.25^2/2}}$$

$$ES = \frac{2.7}{\sqrt{3.52/2}}$$

$$ES = 2.03$$

With the effect size calculated ( $ES \approx 0.4463$ ), we can use the formula for the sample size mentioned earlier:

$$n = \frac{2 \left( \frac{Z\alpha}{2} + Z\beta \right)^2 \cdot (\sigma_1^2 + \sigma_2^2)}{ES^2}$$

Where  $\frac{Z\alpha}{2}$  is the critical value corresponding to the alpha significance level /2 to  $\alpha = 0.025$ ,  $\frac{Z\alpha}{2} \approx 2.81$

and  $Z\beta$  is the critical value corresponding to the statistical power beta to  $\beta = 0.90$ ,  $Z\beta \approx 1.28$

The other values we have are the same:

- Mean of group 1 ( $\mu_1$ ) = 6.1 days
- Standard deviation of group 1 ( $\sigma_1$ ) = 1.4 days
- Mean of group 2 ( $\mu_2$ ) = 3.4 days
- Standard deviation of group 2 ( $\sigma_2$ ) = 1.25 days

Effect size ( $ES$ )  $\approx 20.03$  (previously calculated)

Substituting these values into the formula:

$$n = \frac{2 (2.81 + 1.28)^2 \cdot ((1.40)^2 + (1.25)^2)}{(2.03)^2}$$

$$n = \frac{2 (4.09)^2 \cdot (1.96 + 1.56)}{4.13}$$

$$n = \frac{2 (16.72) \cdot (3.52)}{4.13}$$

$$n = \frac{(35.35) \cdot (3.52)}{4.14}$$

$$n = 30.29$$

Rounding:

$$n = 31 \text{ by each group}$$

To the estimated 31 patients per arm, an extra 20% (6 patients per arm) is added to minimize the loss of statistical power in case patients withdraw from the study or there are missing data.

The sample size has also been determined based on the magnitude of the expected effect of mobilization within 48-72 hours of mechanical ventilation, as suggested in the reference study (33), which justifies our choice to evaluate early mobilization at 24 hours versus 72 hours after mechanical ventilation in our study.

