Variables that could act as confounding factors will be evaluated through a second multiple regression model. In this model, the potentially confounding variable will be removed, and the resulting slope or estimator (adjusted estimate) will be calculated. If there is a change greater than 15%-20%, the confounding variable will be included in the final model. Otherwise, the most parsimonious model will be chosen.

To evaluate the interaction between two variables, another regression model will be performed, including a new variable resulting from multiplying the two potentially interacting variables. If the regression coefficient of this new variable has a significance level of less than 0.05, it is concluded that there is an interaction, and this variable will be included in the model. Variables with potential interaction will be identified by evaluating confounding factors. Researchers will also evaluate clinical variables that may be considered as interaction or confounding variables through the above-described strategy.

The assumption of proportional hazard will be evaluated using Schoenfeld residuals, and influential values will be analyzed through residuals versus observations plots. Multicollinearity will be assessed through matrix curves.

Logistic regression models will be used to assess the relationship between our dichotomous variables, such as failed extubation, post-extubation NIV, prolonged mechanical ventilation, tracheostomy, and dysphonia, and the other studied variables. The assumptions of a logistic regression model, such as linearity in the log of the odds, independence of errors, homogeneity of variance, absence of multicollinearity, absence of outliers, and proportionality of effects, will be evaluated through residual analysis and graphical diagnostics, such as Pearson residual analysis or deviance residual analysis.

A multiplicity adjustment strategy will be employed in statistical tests, such as the Bonferroni method, Holm-Bonferroni, or other methods that control the false discovery rate (FDR), to maintain the overall type 1 error rate at an acceptable level.

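### The trial asks for a difference in days of ventilation, but the only effect estimate named for that question is a Cox hazard ratio, which does not give days

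*Protocol*

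**What the plan says.** **The question is in days.** The general objective (Summary; repeated in section 5) is "To evaluate the difference in days of invasive mechanical ventilation between early multimodal therapy and late multimodal therapy". The hypotheses in section 5 concern the number of days ventilated. Section 6.3 sizes the trial on two means: "the mean number of days of mechanical ventilation in patients with usual physical therapy was" 6.1 (SD 1.4) days, against 3.4 (SD 1.25) with early therapy. Section 6.10 counts the trial as a possible failure if mean duration does not differ significantly.

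**The named answer is a hazard ratio.** The Summary says "To answer this question, we will perform a survival analysis and Cox regression". It then specifies a univariable Cox model with arm as the covariate, a survival curve and a log-rank test. Section 6.13 repeats this.

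**The safeguard is a check of proportionality.** The Summary has "Compliance with the assumption of risk proportionality will be evaluated using Schoenfeld residuals", and section 6.13 has "The assumption of proportional hazard will be evaluated using Schoenfeld residuals". No hazard ratio, event count or distribution of ventilation days is stated.

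**The contrast is one of timing.** Section 3 says "The comparator differs from the study intervention only in the moment" at which therapy starts. Sections 6.1 and 6.5 put the late start at 72 hours.

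**The concern.** A log-rank test gives a p-value and no effect size. A Cox model gives the relative rate of extubation among patients still ventilated. Neither says how many days early therapy saves, which is what the objective, hypotheses and failure criterion ask for. The survival curve carries that information, but no between-arm summary of it is planned.

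A second doubt adds to this. The arms are treated differently only until the late arm starts, so the hazard ratio may not be constant. If it is not, the Cox estimate is an average that depends partly on follow-up and censoring. At stake is a trial whose main reported number does not answer its own question.

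**Working it through.** **Inputs.** From section 6.3: late-arm mean 6.1 days (SD 1.4), early-arm mean 3.4 (SD 1.25). From sections 3 and 6.6: a day-28 horizon, used there for secondary outcomes. Assumed, because the protocol gives none: a hazard ratio of 1.5 and four shapes for late-arm durations.

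**The plan's own figure.** There is no planned hazard ratio to reproduce. The planned effect size is on the scale of means: (6.1 − 3.4) / √((1.4² + 1.25²)/2) = 2.7/1.327 = 2.03, which matches the printed 2.03 (the printed formula shows a minus sign where a plus is needed). The sample-size arithmetic in 6.3 has other faults, but this point does not depend on them.

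**Step 1: days implied by a constant hazard ratio.** Under exact proportional hazards, S_early(t) = S_late(t)^1.5. The difference in restricted mean days is the integral from 0 to 28 of S_late(t) − S_late(t)^1.5. Each late-arm distribution has mean 6.1 before truncation.

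| Assumed late-arm shape | Late, mean to day 28 | Early, mean to day 28 | Difference (days) |
|---|---|---|---|
| Normal, SD 1.4 | 6.10 | 5.62 | 0.5 |
| Weibull, shape 2 (scale 6.88) | 6.10 | 4.98 | 1.1 |
| Exponential | 6.04 | 4.06 | 2.0 |
| Weibull, shape 0.7 (scale 4.82) | 5.68 | 3.37 | 2.3 |

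For the exponential: 6.1 × (1 − e^(−28/6.1)) = 6.04, and (6.1/1.5) × (1 − e^(−28 × 1.5/6.1)) = 4.06. The same hazard ratio covers more than a fourfold range of days, with no departure from proportionality.

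**Step 2: do the planning figures contradict proportional hazards?** The ratio is HR(t) = [f_early(t)/S_early(t)] / [f_late(t)/S_late(t)], with each family matched to the four planning figures.

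| Family | Day 3 | Day 6 |
|---|---|---|
| Normal | 0.485/0.0249 = 19.5 | 1.955/0.538 = 3.6 |
| Weibull (shapes 2.96 early, 4.99 late) | 15.5 | 3.8 |
| Gompertz | 12.0 | 10.9 |

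The Gompertz hazards are 0.002263·e^(0.887t) late and 0.03019·e^(0.853t) early, so HR(t) = 13.34·e^(−0.0341t). A single Gompertz baseline with an exactly constant ratio of 12.2 gives 6.1 (SD 1.40) late and 3.4 (SD 1.22) early, against a planned early SD of 1.25. Two means and two SDs therefore do not settle whether the ratio is constant.

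**The case against.** **Results in days will exist anyway.** The plan compares continuous variables by t-test or Mann-Whitney, days of ventilation is a listed variable, and ventilator-free days to day 28 is a secondary outcome. So it would be wrong to infer that the trial has no result in days. But the t-test line is generic and not tied to the primary objective, and it takes no account of whether a patient was ever extubated. The Mann-Whitney test yields no mean difference. Ventilator-free days are set to 0 at death, so they measure something else.

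**The analysis plan may supply the estimate.** A separate SAP could name a summary in days or a fallback for failed proportionality, and the lack of those details here is no fault. What remains is that the protocol fixes its answer to the primary question on a scale other than that of its objective.

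**Stronger readings that the document does not support.** A reader might infer from 6.3 that the hazard ratio must fall steeply, so that a Cox estimate has no meaning. That needs normal or similar durations, which the protocol never assumes; it plans a Shapiro-Wilk test of the distribution. The steepest part of such a fall also lies where late-arm extubations are almost absent: about 0.5 of 37 by day 3 under the normal model. A reader might also take the 72-hour start as proof of non-proportionality. It fixes exposure, not effect: the benefit of earlier rehabilitation could be delayed or persist. Nor can one say that the Schoenfeld check will usually mislead. That presupposes a violation, and in simulated trials of 31 per arm an approximate version flagged between 10% and 59% of trials, depending on the assumed shape.

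**Conclusion.** The mismatch of scale stands. Objective, hypotheses, sample size and failure criterion are in days, while the only effect estimate named for the primary question is a hazard ratio. Its size: a constant hazard ratio of 1.5 is compatible with roughly 0.5 to 2.3 fewer days to day 28. That range rests on an assumed hazard ratio, assumed shapes and the 6.1-day mean in 6.3; other assumptions would move it, but not the conclusion that the ratio alone does not determine days.

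Proportional hazards is a fair question given the timing contrast, but it is neither refuted nor established by the protocol's figures. The Schoenfeld sentence is not an error. The Cox model and log-rank test are reasonable for time to extubation and need not be removed. This is an inexpensive improvement that lets the trial answer its own question.

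**What to change.** In the Summary and section 6.13:

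- Keep the log-rank test and name it as the primary test.
- State that, whatever the Schoenfeld result, the estimate answering the general objective is the between-arm difference in restricted mean days from intubation to extubation up to day 28, with a 95% confidence interval.
- Report the Cox hazard ratio and the survival curves alongside.
- State how deaths before extubation enter this estimate. If they are censored, the area under the curve is not the number of days actually spent ventilated, and the text should say so.

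The cost is a few sentences and a standard software routine, with no extra data or patients. Because the log-rank test is retained, the test and its power do not change. There are two small drawbacks: the day-28 truncation must be fixed in advance, and the log-rank p-value and the restricted-mean interval can occasionally disagree, so the text should say beforehand that the log-rank test decides significance and the restricted mean gives the size of the effect.

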## 2. Problem Statement and Justification

Patients under mechanical ventilation (MV) in the intensive care unit (ICU) exhibit high hospital mortality rates, ranging from 23% to 51%. This mortality is linked to the success of weaning and the incidence of nosocomial infections. Prolonged MV can increase complications in critically ill patients, extending immobility and raising the risk of ventilator-associated pneumonia, further restricting patients. It is argued that early mobility improves MV-related outcomes, such as ventilator duration and ventilator-free days, breaking the vicious cycle of prolonged MV and immobilization. Additionally, early rehabilitation is associated with reduced morbidity and mortality, as well as complications of the disease, ICU length of stay, hospital stay, and rehospitalization rate. Therefore, weaning from MV through early rehabilitation is crucial to improving the prognosis of ICU patients.

Despite the growing evidence on the utility of early rehabilitation for critically ill patients, programs and interest in outcomes vary among studies. Given this diversity, healthcare professionals must assess whether different programs have a similar therapeutic effect and ensure that the prescribed rehabilitation provides benefits consistent with previous literature. Besides the heterogeneity among programs, different countries and institutions face barriers to implementation, such as a shortage of trained rehabilitation personnel and a cultural gap in the ICU. In cases of personnel

shortages and settings with conservative ICU ethics, early rehabilitation is adapted to a sustainable level, including modified programs or less frequent visits.

Regarding post-intensive care syndrome (PICS), it was established as a syndrome encompassing new or worsened limitations in physical, cognitive, or mental health status that persist beyond acute hospitalization. The goal is to initiate improvements for ICU survivors and their families throughout the continuum of care. Since the creation of PICS in 2010, observational studies have evaluated factors associated with this syndrome; however, few intervention studies have addressed its prevention. Physical therapy with early rehabilitation is considered integral to the multidisciplinary management of ICU patients. Although exercise has been shown to improve strength and function in other populations, reducing inflammation and affecting oxidative stress, a systematic review on the effectiveness of early rehabilitation to prevent PICS in ICU patients has not yet been conducted. The objective of this systematic review is to evaluate the effectiveness of early rehabilitative interventions in preventing PICS in ICU patients.

To our current knowledge, no studies have evaluated the impact and safety of early (within 24 hours) physical therapy, respiratory therapy, speech therapy, and occupational therapy (multimodal therapy). Therefore, our objective is to assess whether multimodal therapy can reduce the days of invasive mechanical ventilation in critically ill patients. This question is relevant given the growing interest in rehabilitation and improving outcomes in these patients. By addressing this question, we hope to contribute to the knowledge of best practices for the care of critically ill patients and improve their long-term outcomes.

### 3. Research question

Does the use of early multimodal therapy reduce the days of invasive mechanical ventilation in adult patients compared to late multimodal therapy?

PICOT strategy

|              |                                                                                                                                                                                                                          |
|--------------|--------------------------------------------------------------------------------------------------------------------------------------------------------------------------------------------------------------------------|
| Population   | Adults ( $\geq 18$ years) hospitalized in the adult intensive care unit of the Santa Fe Foundation in Bogotá who require invasive mechanical ventilation through an endotracheal tube for a period greater than 24 hours |
| Intervention | Early multimodal therapy (<24 hours from intubation) is defined as the set of therapeutic maneuvers performed by the physiotherapy, speech therapy, respiratory therapy, and occupational therapy group at the time      |

Association between early multimodal therapy and days of mechanical ventilation in the intensive care unit of the Fundación Santa Fe de Bogotá: A randomized controlled clinical trial.

Version 6.0

Fundación Santa Fe de Bogotá

April 8, 2024

|            |                                                                                                                                                                                                                                                                                                                                                                                                                                                                                                                                                                                                                                                                                                                                                                                                                                                                                                                                                                                                                                                 |
|------------|-------------------------------------------------------------------------------------------------------------------------------------------------------------------------------------------------------------------------------------------------------------------------------------------------------------------------------------------------------------------------------------------------------------------------------------------------------------------------------------------------------------------------------------------------------------------------------------------------------------------------------------------------------------------------------------------------------------------------------------------------------------------------------------------------------------------------------------------------------------------------------------------------------------------------------------------------------------------------------------------------------------------------------------------------|
|            | orotracheal intubation is performed. The intervention will be carried out exclusively during the stay in the ICU.                                                                                                                                                                                                                                                                                                                                                                                                                                                                                                                                                                                                                                                                                                                                                                                                                                                                                                                               |
| Comparator | Late multimodal therapy is defined as the initiation of multimodal therapy 3 days or more after the start of mechanical ventilation. The comparator differs from the study intervention only in the moment (time from orotracheal intubation to the start of multimodal therapy) of initiation of therapy.                                                                                                                                                                                                                                                                                                                                                                                                                                                                                                                                                                                                                                                                                                                                      |
| Outcomes   | 
Effectiveness
 
Primary outcome: Number of days with invasive mechanical ventilation in the ICU
 
Secondary outcomes:
 
 
• Days free of mechanical ventilation until day 28
 
• Days of delirium until day 28
 
• Time in ICU with delirium until day 28
 
• Days of hospitalization with delirium until day 28
 
• Sedation days until day 28
 
• Sedation-free days until day 28
 
• Barthel index at discharge
 
• Days of hospital stay
 
• Length of stay in ICU
 
• Mortality from any cause up to 90 days
 
• Time from intubation to start of therapy
 
• Muscle strength measured with the medical research scale council (MRC)
 
• Dysphagia at 72 hours
 
• Time until initiation of oral administration
 
• Development of healthcare-associated pneumonia,
 
• Maximum mobility measured by JH-HLM
 
• Grip strength
 
• Extubation failure
 
 |

|      |                                                                                                                                                                                                                                                                                                                                                                                                                                                                                                                                                                                                                                                                                                                                                                                                                                             |
|------|---------------------------------------------------------------------------------------------------------------------------------------------------------------------------------------------------------------------------------------------------------------------------------------------------------------------------------------------------------------------------------------------------------------------------------------------------------------------------------------------------------------------------------------------------------------------------------------------------------------------------------------------------------------------------------------------------------------------------------------------------------------------------------------------------------------------------------------------|
|      | 
 
• Need for non-invasive mechanical ventilation
 
• Cognitive function is measured using the Montreal Cognitive Assessment (MOCA)
 
• Quick sensitivity and dexterity test
 
 
Security
 
Outcomes
 
 
• Number of adverse events 
 
○ Altered blood pressure
 
○ Cardiac arrhythmia
 
○ oxygen desaturation
 
○ Pain or agitation
 
○ Invasive line removal
 
○ Gastrointestinal (nausea, vomiting, or diarrhea)
 
○ tachypnea
 
○ Altered neurological status
 
 
 
• Number of serious adverse events
 
• Unscheduled extubation
 
• Healthcare-associated pneumonia
 
• Bronchoaspiration
 
 |
| Time | 
Screening: Verification of the inclusion and exclusion criteria of patients will take a maximum of 24 hours after endotracheal intubation.
 
Intervention: For both study groups, multimodal therapy will be applied exclusively while the patient is in the ICU.
 
Follow-up:
 
At the beginning of the study, the variables described in point 6.6 will be measured.
 
At the time of weaning from ventilatory support, the following variables will be measured: delta POCC, muscle pressure, P0.1, number of secretions per orotracheal tube, asynchrony index, NIF, % leak, peak cough flow, measurement of diaphragmatic excursion,
                                                                                                                                                                        |

|  |                                                                                                                                                                                                                                                                                                             |
|--|-------------------------------------------------------------------------------------------------------------------------------------------------------------------------------------------------------------------------------------------------------------------------------------------------------------|
|  | 
measurement percentage of diaphragmatic thickness, and tracheobronchial secretions.
 
On the day of hospital discharge, the variables recorded in point 6.6 will be measured.
 
The last measurement of variables will be carried out 90 days after the patient is intubated by point 6.6.
 |
|--|-------------------------------------------------------------------------------------------------------------------------------------------------------------------------------------------------------------------------------------------------------------------------------------------------------------|

